**Objective:**

This study aims to determine the optimal deployment of the PPA in clinical settings (at enrollment vs delayed start) and to compare intervention outcomes with a no-intervention, observation-only condition. The PPA is designed specifically for key HIV disparity populations, including younger sexual, gender, racial, and ethnic minorities.

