## Methods

### Study Design

Specific aims and corresponding hypotheses will be evaluated in a randomized controlled trial that compares HIV outcomes in patient groups randomized to either immediate or delayed access to the PPA. The delayed-start design is intended to ensure that both randomized study conditions receive identical study procedures, follow-up, reminders, incentives, and assessments during the first 6 months of participation. The only difference is the timing of app access. Any improvement observed in the delayed-start group during this period can therefore be attributed primarily to nonspecific effects of trial participation. The primary randomized comparison at 6 months thus estimates the incremental benefit of the app beyond these common trial effects. A greater improvement in outcomes in the immediate-start group at this point would provide evidence of a specific impact of the app.

Prospective questionnaires will be administered at baseline and at 3, 6, 9, and 12 months to provide evidence for model-specific hypotheses and the mediating effects of covariates and demographics. We have included an opportunity for patients who decline full study participation to grant permission to the PoPIT team to abstract their HIV outcomes from medical records on the same schedule as full study participants. This observation-only arm includes only the baseline questionnaire and medical record review of study outcomes. The inclusion of an observational cohort in the randomized controlled trial design strengthens external validity by enabling comparison of trial participants with the broader clinic population. By comparing outcomes from both randomized controlled trial arms with those of the observational cohort, we will gain additional insight into how trial participation may influence outcomes and how the intervention might be further adapted for a more diverse clinical population.

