### Enrollment, Randomization, and Data Collection Procedures

All participants are consented, enrolled, and randomized at the partner institution where they receive care, in partnership with the PoPIT staff, who are needed to set up the user’s PPA account. Specifically, following in-person consent at the partner site, all participants complete a preloaded baseline questionnaire on a study-dedicated tablet in the presence of study staff. While they are completing the questionnaire, the trial participant is randomly assigned in REDCap to either the intervention (immediate PPA start) or control (6-month delayed PPA start) arm at a 1:1 ratio. Participants randomized to the delayed-start arm receive usual clinic care before beginning the clinical intervention. Given our pilot findings indicating a stronger PPA effect on HIV viral suppression among participants in the youngest age group (ie, <24 years), we employ a block randomization strategy in which study arm assignment occurs separately for participants within the age groups 13-24 and 25-34 years.

Following randomization, site study staff assist participants randomized to the immediate-start arm in downloading the PPA from the public app store using the participant’s personal phone. Site study staff guide participants through in-app tutorials demonstrating how to use app features. Participants randomized to the delayed-start arm are provided with a folder containing general HIV self-management information and contact numbers for the clinic and the site coordinator. Data are collected via online forms (enrollment and medical record review), questionnaires, and SMS text messaging. Participants are consented and enrolled by study staff in person, and the baseline questionnaire is completed independently at the same visit. Remaining follow-up questionnaires at 3, 6, 9, and 12 months are prompted by an SMS text message or email and completed online. Participants and study staff are aware of study arm assignment. Delayed-start participants are given app access after completing the 6-month questionnaire. Site study staff follow the same procedure to assist with downloading the app and reviewing tutorials for participants in both the immediate- and delayed-start arms.

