#### Clinical Outcomes

Retention in HIV care and viral suppression are measured using standardized performance measures developed by the HRSA/HIV/AIDS Bureau [89]. Measures selected for this study are retention in HIV medical care (2 or more visits separated by at least 90 days for HIV care within the measurement year) and HIV load suppression (the most recent viral load <200 copies/mL during the measurement year). Values for outcome variables (engagement in care and viral suppression) are derived from a retrospective medical record review conducted by site study staff using a study-specific form. Engagement in care is determined by at least one office visit with an HIV clinician per 6-month interval for 12 months before and 6 months after study enrollment. Viral suppression is determined by assessing the participant’s viral load, as noted in laboratory values, typically required at least every 6 months per the standard of care. A value of <200 copies/mL is considered suppressed. Values for each variable are established for the year before study enrollment, at baseline enrollment, and then at 6-month intervals for 18 months.

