### Power Analysis

Group sample sizes of 106 in the Positive Peer group and 106 in the control group achieve 90% power to detect a difference between group proportions of 0.20. This is the minimum sample size required in each group to detect the desired difference in proportions. The proportion in group 1 (the treatment group) is assumed to be 0.60 under the null hypothesis and 0.80 under the alternative hypothesis. The proportion in group 2 (the control group) is 0.60. The test statistic used is the 2-sided *Z* test with pooled variance. The significance level of the test was set at .05. Several assumptions regarding baseline viral suppression were tested based on the literature. The current sample size is based on 63% viral suppression at baseline and a planned 80% in the intervention group. If baseline viral suppression is lower, a smaller sample size would be needed to demonstrate a 20% improvement in viral suppression. Based on this estimation, we aim to recruit and randomize 250 eligible individuals to the study from 6 clinic sites over 24 months, allowing for potential loss to follow-up. It is important to note that patients without documentation of a clinic visit during the assessment period are designated as out of care and will be assumed to be HIV virally unsuppressed. Available data on other outcomes and covariates, however, will be handled using mixed-effects models, which employ maximum likelihood estimation and assume missing-at-random patterns to support valid inferences.

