### Planned Statistical Analysis

Aims 1 and 2 entail data collection and analysis to provide evidence of PPA effectiveness. Outcomes include retention in HIV care (proportion of enrolled patients with laboratory results in each 6-month period of the study), HIV load suppression (proportion of enrolled patients whose viral load measurement at 6 months in the study is <200 copies/mL), as well as self-reported psychosocial variables, specifically perceived technology affordances, attitudes toward technology, and self-efficacy for managing chronic conditions. We expect that key demographics, technology covariates, and PPA use will predict self-efficacy, which will be directly associated with (1) retention in care, (2) viral suppression, and (3) HIV-related perceived stigma. Additionally, we plan to test potential covariate mediation and examine theoretical linkages in our model of PPA effects.

Analyses of repeated measures will be performed using generalized linear mixed-effects models with a logit link function for binary outcomes (ie, viral suppression and engagement in care) and linear mixed-effects models for continuous outcomes (eg, perceived stigma, resilience). Time will be treated as a fixed, repeated factor within patients, and patient-specific random effects will be included to account for within-patient correlation. To appropriately model the hierarchical structure of observations nested within patients and patients nested within sites, the site will be included as a random effect, providing an estimate of between-site variability. Multilevel mediation models will be used to evaluate potential mediating effects of covariates. *P* values will be adjusted using Bonferroni or Benjamini-Hochberg correction procedures to control the family-wise type I error rate due to multiple comparisons across distinct psychological outcomes.

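### The stated model for viral suppression is not tied to the powered 6-month difference in proportions, and it names neither the age stratum nor baseline suppression

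*Protocol article*

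**What the plan says.** All references are to the protocol article.

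- **Primary comparison.** Study Design places it at 6 months: "The primary randomized comparison at 6 months thus estimates the incremental benefit of the app beyond these common trial effects". The Abstract's Objective adds a deployment question, which is to "determine the optimal deployment of the PPA in clinical settings (at enrollment vs delayed start").
- **Endpoint.** Planned Statistical Analysis lists "HIV load suppression (proportion of enrolled patients whose viral load measurement at 6 months in the study is <200 copies/mL").
- **Powered quantity.** Power Analysis says that 106 per group "achieve 90% power to detect a difference between group proportions of 0.20", taking 0.60 in controls and 0.80 with the app and using a two-sided Z test at the .05 level.
- **Stated model.** Planned Statistical Analysis gives a generalised linear mixed model with a logit link for the binary outcomes. On its terms it says: "Time will be treated as a fixed, repeated factor within patients, and patient-specific random effects will be included to account for within-patient correlation". Site is a random effect.
- **Randomisation.** Enrollment, Randomization, and Data Collection Procedures describes a "block randomization strategy in which study arm assignment occurs separately for participants within the age groups 13-24 and 25-34 years", chosen because the pilot effect on suppression was stronger in the youngest. The same section gives the delayed-start arm the app after the 6-month questionnaire.
- **Data available.** Clinical Outcomes: "Values for each variable are established for the year before study enrollment, at baseline enrollment, and then at 6-month intervals for 18 months".

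**The concern.** The powered quantity and the stated analysis are on different scales, and nothing in the article links them. Power is for a marginal difference in proportions at one visit. The model's natural output is a subject-specific log odds ratio from repeated visits. The powered Z test does not reappear in the analysis section, and no arm-by-time term, 6-month contrast or conversion to a difference in proportions is mentioned. A reader given only the model coefficient could not say whether the 20-point target was met.

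Two smaller matters follow from the same paragraph. Age group defines the randomisation strata, and baseline suppression is recorded and is plausibly a strong predictor of later suppression, yet neither is named as a term for this outcome. Also, outcomes run to 18 months while controls have the app after month 6. The later visits therefore answer early versus late start, not app versus no app, and should not share one arm effect with the 6-month visit.

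**Working it through.** **1. The plan's own figure.** Inputs from Power Analysis: 0.60 versus 0.80, two-sided alpha .05, 90% power.
- Unpooled Z: n = (1.960 + 1.282)² × (0.60×0.40 + 0.80×0.20) / 0.20² = 105.07, so 106 per arm, with power 90.2%.
- Pooled Z, which is the variance the text names: 109 per arm, with power 89.4% at 106.

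The stated figure is reproduced within rounding of method, and the powered quantity is confirmed as a 6-month difference in proportions. With 250 randomised (125 per arm), simulated power for that contrast is about 94%.

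**2. Effect scale.** The marginal odds ratio for 80% versus 60% is (0.80/0.20) / (0.60/0.40) = 4 / 1.5 = 2.67. In a random-intercept logit model with SD s, the conditional intercepts b0 and b1 solve E[expit(b0 + sZ)] = 0.60 and E[expit(b1 + sZ)] = 0.80, with Z standard normal. The conditional odds ratio is exp(b1 − b0). The article gives no SD, so a range is assumed (values by numerical quadrature):

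| Assumed SD | Conditional odds ratio |
|---|---|
| 0 | 2.67 |
| 1 | 3.19 |
| 1.5 | 3.83 |
| 2 | 4.76 |
| 3 | 7.76 |

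Every row is the same 20-point difference. The coefficient depends on between-patient spread, so it does not map to the target unless it is averaged over the random effects.

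**3. Age stratum.** Assume two equal strata and a 20-point effect in each. The stratified variance is the mean over strata of p0(1−p0) + p1(1−p1), and power = Φ(0.20/√(variance/106) − 1.96).
- No age difference: variance 0.40, power 90.2%.
- Control rates 55% and 65%: variance 0.395, power 90.6%. The unadjusted test has a true type I error of about 4.9%.
- Control rates 50% and 70%: variance ½(0.25+0.21) + ½(0.21+0.09) = 0.38, power 91.6%. The unadjusted type I error is about 4.5%.

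Omitting age therefore costs about 0 to 1.5 points of power and is slightly conservative.

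**4. Baseline suppression.** The article gives no association between baseline and 6-month suppression, so this too must be assumed. Simulation at 60% versus 80% and 106 per arm gave about 1 to 5 points of power from adjustment. The formula in step 3 agrees in size. If baseline status splits controls into equal halves at 45% and 75%, the variance is ½(0.2475+0.2275) + ½(0.1875+0.0475) = 0.355 and power is 93.3%, a gain of about 3 points.

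**5. Later visits.** This is conditional on an analysis that the article does not state. If one arm effect were averaged over 6, 12 and 18 months:
- Full catch-up of controls after month 6: (20 + 0 + 0)/3 = 6.7 points. Simulated power is 30 to 37% at 106 per arm (assumed SD 1.5 to 3).
- Half catch-up: (20 + 10 + 10)/3 = 13.3 points. Simulated power is 77 to 87%.

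**The case against.** The strongest reply is that a journal article condenses the plan. Covariates, contrasts and effect measures are usually set in the SAP, and the list of terms is plainly incomplete, since it does not name the arm either. That stands to this extent: nobody can conclude that age and baseline suppression are excluded, and baseline may already enter as one of the time levels. The point is that the article states a powered quantity and a model without joining them.

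A reader might infer three stronger things, and the documents support none of them.
- *That the model cannot give the powered quantity.* It can. An arm-by-time term gives a 6-month contrast, and averaging over the random effects gives a difference in proportions. With no effect, the conditional and marginal odds ratios both equal 1, so the matter is one of reporting scale and not of test validity.
- *That the plan pools the arm effect over 18 months.* No section says so. Study Design makes the 6-month comparison primary, the endpoint is defined at 6 months, and time as a fixed factor is compatible with visit-specific contrasts. The 18 months come from the data schedule. The 6.7-point figure shows what to rule out; it does not describe the plan.
- *That missing covariates leave the trial with power near 79%.* At 106 per arm that figure (78.7%) comes from using 63% versus 80%, the other pair of rates in Power Analysis. It has nothing to do with covariates.

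**Conclusion.** The point holds as a modest, worthwhile correction. The comparison, endpoint and power calculation all concern a 6-month difference in proportions. The stated analysis yields a conditional odds ratio: about 3.2 to 4.8 for assumed SDs of 1 to 2, against a marginal 2.67. The step from one to the other is not fixed.

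The adjustment gain is small: about 0 to 1.5 power points for age and about 1 to 5 for baseline suppression, all under assumed associations. Naming the 6-month contrast also removes any room to choose, once data are in, an average over visits at which controls already have the app. That choice would matter much more than the covariates, but only if it were made.

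**What to change.** State the primary analysis of viral suppression as the immediate-versus-delayed contrast at 6 months. Estimate it either by logistic regression on the 6-month outcome or by the planned mixed model with an arm-by-time term, taking the 6-month contrast only. Include age group (13-24, 25-34) and baseline suppression as fixed effects, with site as planned. Report a standardised risk difference with 95% CI, so that the result can be set against the 20-point target; the odds ratio can accompany it. Report the 12- and 18-month contrasts separately, labelled as immediate versus delayed deployment.

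The cost is some wording in the SAP and slightly more analysis work. All the variables are already collected, and accrual runs to November 2026, so this can be settled before the comparison is analysed.

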### The Positive Peers Mobile App

PPA is a free, multifunction mobile app that features interactive functions organized around a Mind/Body/Spirit theme. The Mind theme is characterized by information provision, including more than 400 vetted articles concerning issues faced by YPWH, as well as first-person stories from current app users living with HIV. The Body theme offers tangible support in the form of interactive medication and laboratory reminders and trackers, and curated state-by-state community resources addressing a variety of living needs (clothing, housing, food). The Spirit theme fosters human connection through a community forum that allows users to ask questions and share experiences and encouragement, as well as a chat function for 1-on-1 conversations. The app is freely available to eligible young people (ages 13-34) who provide evidence of their HIV-positive status. App activity is monitored and supported by a group of trained app administrators at our home medical institution in Cleveland, Ohio, as well as at key partner locations across the United States.

Following development and successful feasibility testing with a pilot group [17], a cohort comparison medical record review of PPA users and clinically eligible but study-naïve nonusers showed that PPA users were significantly more likely to be regularly engaged in HIV care and to achieve higher rates of viral suppression than nonusers, particularly among young adults aged 13-24 [18]. This success, paired with positive reactions identified in qualitative work [19], provided the basis for planning a randomized controlled trial to evaluate the PPA as a clinical tool for supporting YPWH who are newly diagnosed or seeking care in 6 federally designated Ending the Epidemic priority jurisdictions in the United States [14].

The primary objective of the Positive Peers Intervention Trial (PoPIT) is to evaluate the impact of the mHealth app on engagement in care and viral suppression outcomes among newly diagnosed and reengaged young patients. Study research questions and hypotheses are informed by, and evaluated based on, social networking, media uses and effects, and social support theories.

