### Study Rationale and Objectives

We expect the PPA to support engagement in HIV care by normalizing and rewarding care visits, promoting health literacy, reducing stigma, and enhancing inclusion, thereby allowing users to help others with similar challenges. Our goal is to increase HIV viral suppression rates by at least 15% by offering practical and peer support through a smartphone app. Specific aims addressed by the protocol described in this manuscript are (1) comparing the effectiveness of HIV care supported by the PPA with usual care for improving retention in HIV care and viral suppression among high-priority adolescents and young adults with HIV; (2) identifying factors that predict user engagement with primary PPA components and associated effects on retention in care, viral suppression, and HIV-related perceived stigma; and (3) evaluating PoPIT implementation across sites and over time. Figure 1 illustrates the conceptual model of the PoPIT study’s influence and outcomes. This paper describes the protocol used to achieve these aims in a randomized clinical trial with a concurrent qualitative evaluation focused on user experience.

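### Benjamini-Hochberg is said to control the family-wise error rate across the psychological outcomes; it controls the false discovery rate, so the plan should name one procedure with the property it really has

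*Protocol article*

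**What the plan says.** The multiplicity rule is one sentence at the end of Planned Statistical Analysis. It sets out the treatment of P values as follows: "adjusted using Bonferroni or Benjamini-Hochberg correction procedures to control the family-wise type I error rate due to multiple comparisons across distinct psychological outcomes". Two procedures are offered, one error rate is attached to both, and no rule for choosing between them is given.

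The clinical outcomes are handled elsewhere. The primary objective, in the section on the app, is to "evaluate the impact of the mHealth app on engagement in care and viral suppression outcomes". Aim 1, under Study Rationale and Objectives, again names both, as "improving retention in HIV care and viral suppression among high-priority adolescents and young adults with HIV", without ranking them. The same analysis section models them as "binary outcomes (ie, viral suppression and engagement in care", apart from the psychological outcomes. The Power Analysis section sizes the trial on viral suppression alone: "The significance level of the test was set at .05".

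**The concern.** The family-wise error rate is the chance of at least one false positive in the family. The false discovery rate is the expected share of false positives among the rejections. Benjamini-Hochberg limits the second. The two coincide only when every null is true, because then every rejection is false. This trial expects effects on several psychosocial measures, so the all-null case is not the one it is planned for.

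At stake is what a reader may conclude from an adjusted psychosocial P value. Under Bonferroni, the chance of any false claim in the family is at most 5%. Under Benjamini-Hochberg the report would carry the same sentence, but the chance could be appreciably higher. Because the text joins the two procedures with 'or', the reader cannot tell which guarantee applies.

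**Working it through.** **Plan's own figure.** The multiplicity sentence contains no number to reproduce. The only related figure is the 106 per arm in Power Analysis (0.60 against 0.80, two-sided 0.05, 90% power). The unpooled formula gives (1.960 + 1.282)² × (0.24 + 0.16) / 0.20² = 105.07, rounded up to 106. The pooled version gives 109, and 106 per arm has 89.4% power. The figure is not in dispute here.

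**Hand check of Benjamini-Hochberg.** Take four independent outcomes, two with effects large enough always to be detected and two true nulls. The third step of the procedure has cut-off 0.05 × 3/4 = 0.0375 and the fourth has 0.05. A false positive occurs if at least one null P value is at or below 0.0375, or if both lie between 0.0375 and 0.05:

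1 − (1 − 0.0375)² + (0.05 − 0.0375)² = 0.0736 + 0.0002 = 0.074.

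The family-wise error is 7.4%. Bonferroni tests each null at 0.05/4 = 0.0125, so its error is 1 − 0.9875² = 2.5%.

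**Range by simulation.** The assumptions are mine, because the article does not list the family:
- Number of outcomes: 3 to 5 if each construct counts once (affordances, attitudes, self-efficacy, then stigma and social support). If subscales count separately, Table 3 gives 4 stigma + 4 self-efficacy = 8, or 11 with the 3 social-support subscales.
- About half the nulls true.
- Real effects at 90% unadjusted power, a z-shift of 1.960 + 1.282 = 3.24.
- Correlation between test statistics 0 or 0.5; 200,000 replicates per setting.

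| Outcomes (true nulls) | Benjamini-Hochberg, corr. 0 | Benjamini-Hochberg, corr. 0.5 | Holm, corr. 0 | Bonferroni, corr. 0 |
|---|---|---|---|---|
| 3 (2) | 6.2% | 5.5% | 4.7% | 3.4% |
| 4 (2) | 6.8% | 5.9% | 4.3% | 2.5% |
| 5 (3) | 7.9% | 6.5% | 4.3% | 2.9% |
| 8 (4) | 10.6% | 7.9% | 4.0% | 2.5% |
| 11 (6) | 13.2% | 9.3% | 3.9% | 2.7% |

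Entries are family-wise error rates. Two boundary cases show no excess. With all nulls true, Benjamini-Hochberg gives about 5% (8 outcomes, independent: 5.0%). With a single true null it also stays below 5% (3 outcomes, one null: 4.7%). In every setting its false discovery rate was at or below about 5%, which is the property it does have.

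**Clinical outcomes.** If success were claimed on either engagement in care or suppression, each tested at 0.05, the family-wise error would be 1 − 0.95² = 9.75% under independence. By simulation it is 9.5% at correlation 0.3, 9.1% at 0.5 and 7.8% at 0.8. Independence is unlikely, because Power Analysis counts patients with no documented visit as unsuppressed. If suppression is thereby nested within being in care, the correlation is √[p_s(1 − p_c) / (p_c(1 − p_s))]. With 60% suppressed and an assumed 70% in care this is √(0.18/0.28) = 0.80; with an assumed 90% in care it is √(0.06/0.36) = 0.41.

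**The case against.** The strongest reply is that this is a wording slip confined to psychosocial outcomes. Bonferroni is one of the two options, and under it the sentence is true. The powered comparison on viral suppression is untouched. For a family of three to five correlated outcomes the excess over 5% is one or two percentage points, and the larger figures need subscales to be counted as separate, independent outcomes. All of this stands and sets the weight of the point. It does not make the sentence true for Benjamini-Hochberg, and an analysis plan that is not shown could not do so either.

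Three stronger readings are tempting, and the article does not support them:

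- A reader might infer that the choice between the procedures will be made after the P values are seen. The article is silent on when the choice is made, and an analysis plan may fix it beforehand.
- A reader might infer that the psychosocial claims lack type I error control altogether. They lack it only if Benjamini-Hochberg is the procedure used.
- A reader might infer that the two clinical outcomes are uncontrolled co-primaries with nearly double the nominal error. No section states a rule of success on either at 0.05. The quoted significance level belongs to one power calculation, for suppression, which itself suggests a lead outcome. An analysis plan may settle the ranking, and 9.75% is a ceiling that assumes independence.

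What remains of the clinical part is a request for clarity: both outcomes sit unranked in the primary objective and in Aim 1, while only one is powered.

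**Conclusion.** The point holds for the error property. The article attributes family-wise control to a procedure that controls the false discovery rate. The statement fails if Benjamini-Hochberg is used, at least two outcomes are truly null and others have real effects; it holds under Bonferroni. Under the assumptions set out above, the family-wise error would be about 5.5-8% for 3-5 outcomes and 8-13% for 8-11, against below 5% for Holm. These ranges depend on an assumed family size, effect size, share of true nulls and correlation, none of which the article gives.

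The ranking of the clinical outcomes is a secondary clarification, not an established error. If success on either at 0.05 were ever claimed, the family-wise error would be roughly 7.8-9.75%, depending on their correlation. Overall this is a should-fix item, with no bearing on the sample size.

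**What to change.** List the psychosocial outcomes that form the family, and name one procedure before any outcome data are analysed. Either option makes the sentence correct:

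1. **Holm at 0.05**, described as controlling the family-wise error rate. It does so under any dependence and is never less powerful than Bonferroni.
2. **Benjamini-Hochberg at 0.05**, described as controlling the false discovery rate, with the reference to family-wise error removed.

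The second costs only a change of wording and a weaker claim. The first costs some rejections relative to Benjamini-Hochberg, and more as the family grows. In the independent simulations above, the average power per real effect was 79.7% for Holm against 83.3% with 4 outcomes, and 73.2% against 82.9% with 8. Counting constructs rather than subscales keeps this cost small.

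Add one sentence stating that 6-month viral suppression is the primary outcome and that retention is tested at 0.05 only if suppression is significant. This fixed sequence keeps the full 0.05 for suppression and needs no extra participants. Splitting alpha to 0.025 each would instead need 129 per arm for 90% power at 0.60 against 0.80, compared with 250/2 = 125 planned. If the analysis plan already makes these choices, it is enough to bring the article's sentence into line with it.
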